### Universal study requirements and adherence promotion strategies

3.3

Consumption of deep-sea fish oil and other omega-3 fatty acid supplements is prohibited for the duration of the trial.

Strategies to enhance intervention adherence will mainly include the following: (1) Ensuring timely supply and accessibility of eggs. Eggs will be delivered weekly to the dining center of the community health service center (CHSC) nearest to the participants. For elderly participants who cannot collect eggs daily from the CHSC, eggs will be mailed or delivered to their homes on a weekly basis. These measures will prevent adherence interruptions caused by delayed delivery of the intervention eggs. (2) Ensuring appropriate cooking methods. Eggs will be boiled or steamed daily at the CHSC dining center, and elderly participants will collect and consume them every morning. For participants receiving home delivery, instructions on boiling or steaming eggs will be included with each delivery, reminding them to use these methods rather than frying or other cooking methods. (3) Targeted reminders and supervision. Each elderly participant will be assigned a researcher responsible for follow-up and reminders. Reminders will be delivered via telephone follow-up (once weekly) combined with smartphone/WeChat messages (daily timed push notifications). Traditional telephone reminders will be retained for those unfamiliar with smart devices. Family members or primary caregivers living with the elderly participants will be invited to participate in “monitor” training to assist with reminders and daily observation. A consumption log will be provided, and participants will check off each date upon consuming one egg, creating a visual completion prompt. (4) Implementing behavioral interventions and incentives. Participants will be instructed to consume eggs at breakfast to leverage the regularity of breakfast habits and improve execution stability. Participants will be provided feedback on changes in relevant biomarker levels (e.g., Omega-3 Index) to enhance motivation through biomarker visualization. Participants will be allowed flexibility in scheduling consumption within a week (e.g., consuming on Thursday if missed on Wednesday), but strict prohibition against consuming ≥2 eggs in a single sitting will be enforced to avoid overconsumption.

For monitoring and assessing intervention adherence, the following methods will be employed: (1) Subjective assessment methods: The 3-day 24-h dietary recall and Food Frequency Questionnaire (FFQ) will be used to record egg consumption timing, quantity, and accompanying foods, with cross-validation between the two methods. Trained interviewers will conduct telephone follow-ups weekly using open-ended questions such as: “What did you eat for your three meals yesterday? Did you consume an egg? At what time?” (2) Objective assessment methods: Fasting venous blood samples will be collected to measure biomarkers of omega-3 fatty acid intake, specifically the Omega-3 Index (the percentage of EPA and DHA in total fatty acids in red blood cell membranes). (3) Process monitoring: Empty egg packaging from the previous week will be collected, and remaining egg counts will be verified against self-reported consumption.

Through this three-tier adherence management system (supply guarantee, reminder supervision, and biological verification), we will maximize the assurance, supervision, and monitoring of stable egg consumption behavior among elderly participants during the 12-week intervention period, thereby enhancing the internal validity of the study.

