Regular eggs group: Participants will consume one regular egg daily, five days per week (Tuesday through Saturday) for 12 weeks. Participants will consume eggs uniformly in the morning to ensure intervention standardization. Eggs will be provided by a centralized supplier along with product quality inspection reports. Nutritional analyses for eggs used in the intervention and control groups will be conducted by the research team.

Blank control group: Participants will maintain their habitual dietary patterns throughout the 12-week study period.

In addition, during the subsequent intervention period, regular testing of omega-3 and other components in each group will be performed to verify and ensure that the intervention dose is clear and reproducible. This study will allow participants to consume other foods containing omega-3 fatty acids, provided that detailed records are maintained in dietary logs. Dietary intake will be assessed using the Food Frequency Questionnaire (FFQ) combined with 3-day 24-h dietary recalls. Participants will be required to provide particularly detailed documentation of omega-3-rich foods. During data analysis, these dietary records will be rigorously analyzed to evaluate their potential impact on the study outcomes.

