### Blinding method

4.3

An open-label control with blinded intervention arms design will be adopted in this study. Of the three randomly allocated groups, only the blank control group will be unblinded and aware of their non-intervention status. The control group and the omega-3 PUFA-enriched eggs group will be administered using a blinded protocol, where participants will be informed that they will receive egg intervention but will remain blinded to the specific type (regular fresh eggs vs. omega-3 PUFA-enriched eggs). The two egg types will be identical in appearance and distinguished only by coded labels. Blinded personnel will also include intervention administrators, outcome assessors, and data analysts. Throughout the entire trial, intervention administrators, outcome assessors, and data analysts will be informed only of the unique identification codes of the participants and will be unaware of the intervention types corresponding to each group. The random allocation table will be encrypted and stored by an independent third-party biostatistician, and centralized unblinding will be performed only after the trial has been completed and the data have been locked.

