### Key secondary outcomes and exploratory outcomes

5.4

Blood samples will be collected at baseline (Week 0) and Weeks 4, 8, and 12 to assess indicators related to glucose and lipid metabolism (four samples per participant, covering lipid profiles, glucose homeostasis, inflammatory markers, oxidative stress, and other metabolic parameters). Samples will be collected following an overnight fast, with serum and plasma separated according to standardized protocols. Aliquots will be stored at −80 C and shipped in batches for centralized analysis. Biochemical and immunological markers will be quantified using enzyme-linked immunosorbent assay (ELISA) and other validated methods, with rigorous technical support to ensure intra- and inter-assay consistency and full traceability.

Key secondary outcomes:

(1) Lipid metabolism indicators included total cholesterol (TC), triglycerides (TG), high-density lipoprotein cholesterol (HDL-C), low-density lipoprotein cholesterol (LDL-C), free fatty acids (FFA), lipoprotein(a) [Lp(a)], apolipoprotein A1 (ApoA1), and apolipoprotein B (ApoB). These indicators will provide a comprehensive assessment of lipid metabolism disorders and associated cardiovascular risk.(2) Inflammation and oxidative stress markers: Measured indicators will include high-sensitivity C-reactive protein (hs-CRP), interleukin-1 (IL-1), interleukin-6 (IL-6), tumor necrosis factor-alpha (TNF-α), and oxidative stress markers such as superoxide dismutase (SOD) and glutathione (GSH).

Exploratory outcomes:

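### Section 3.3 shows participants their Omega-3 Index changes as an adherence tool, which contradicts the promise in Section 4.3 to keep the two egg arms blinded until data lock

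*Protocol article*

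**What the plan says.** Section 3.3 of the protocol article groups its adherence strategies under four items. The fourth, on behavioural interventions and incentives, contains this commitment: "Participants will be provided feedback on changes in relevant biomarker levels (e.g., Omega-3 Index) to enhance motivation through biomarker visualization". The feedback is not confined to one arm, to markers unaffected by egg type, or to the time after unblinding. Neither its dates nor the person who delivers it is given. The section closes by saying that the adherence system is meant to secure "stable egg consumption behavior among elderly participants during the 12-week intervention period". The same section names the objective adherence marker: "specifically the Omega-3 Index (the percentage of EPA and DHA in total fatty acids in red blood cell membranes".

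Section 4.3 (and the blinding row of Table 1) says of the two egg arms that "participants will be informed that they will receive egg intervention but will remain blinded to the specific type". Intervention administrators, outcome assessors and data analysts are to know only participant codes, and "centralized unblinding will be performed only after the trial has been completed and the data have been locked".

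Section 5.3 makes enriched versus regular eggs the primary comparison. Section 3.2 adds: "This study will allow participants to consume other foods containing omega-3 fatty acids", provided they are logged. Section 5.4 has serum and plasma aliquots frozen and "shipped in batches for centralized analysis".

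**The concern.** The enriched-versus-regular contrast is the only one in the trial with participant blinding, because the blank control is open-label. That blinding rests on eggs that look the same and differ only in coded labels. Identical appearance gives no protection if participants are shown a blood result that the two egg types are meant to move differently.

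Two things are at stake. First, a participant can form a better-than-chance view of which egg they receive, and so can any blinded staff member who sees individual results. Second, even without a guess, the content of the feedback differs by arm: a rising index encourages, a flat one does not. That is a co-intervention that differs between the arms being compared. A regular-egg participant who sees no change may eat more omega-3 foods, which is allowed, or may lose interest and drop out.

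The Discussion (Section 8) treats the limits of blinding at length, including unequal expectations between the arms and behaviour change affecting biochemical outcomes. It does not mention this feedback.

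**Working it through.** The plan gives no figure for this point, so the check sets the sections side by side and adds simple arithmetic for size.

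**1. Can both commitments be carried out?** Section 3.3 gives individual biomarker changes to participants to motivate them during the intervention. Section 4.3 withholds the egg type from the same people until data lock. They are compatible only if the marker carries no information about the arm, or if the feedback comes after the lock.

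**2. Does the marker carry information about the arm?** Section 3.3 defines the Omega-3 Index as a red-cell measure of EPA and DHA and uses it as a biomarker of omega-3 intake. Section 5.2 expects omega-3 measurements to show higher exposure in the enriched arm than in the regular arm. Section 5.2 concerns plasma DHA, EPA and ALA rather than red cells, so the two are related markers, not the same one. On the protocol's own reasoning, some arm difference in the index is expected.

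**3. How strong is the signal?** Section 3.2 gives about 55.5 mg of DHA per enriched egg, five eggs a week:

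55.5 × 5/7 = 39.6 mg of DHA per day on average.

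The DHA content of the regular egg is not given, so the contrast between the egg arms is at most this. The expected change in the index and its SD are not given either. As an illustration, take normal changes with equal SD and a standardised arm difference d (assumed). With the cut-off halfway between the arm means, the chance of a correct guess from one change value is Φ(d/2):

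| d (assumed) | Chance of correct guess |
|---|---|
| 0 | 50% |
| 0.5 | 60% |
| 1 | 69% |
| 1.5 | 77% |
| 2 | 84% |
| 3 | 93% |

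The midpoint is the best possible cut-off with equal arms, so a participant who does not know it would do somewhat worse for the same d.

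**4. How many people, and for how long?** Section 2.3 gives 44 per group: 2 × (1.96 + 0.84)² × 58² / 35² = 43.06, rounded up to 44. With 25% dropout, 44/0.75 = 58.7, so 59, set at 60. This reproduces. The two egg arms hold 60 + 60 = 120 participants. The first sample after baseline is at week 4, so exposure to feedback during treatment is at most 12 − 4 = 8 weeks.

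**5. Would results exist in time?** Section 5.2 stores plasma at −80 °C until analysis, Section 5.4 ships serum and plasma aliquots in batches, and Table 2 lists the laboratory testing phase after the third follow-up. No separate handling is described for the red-cell measure. If this schedule also governs the index, little or no feedback could reach participants during treatment, and the strategy in Section 3.3 could not work.

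**6. By what route could TG be affected?** Fasting TG is a laboratory measure, so knowledge of the arm does not bias the reading itself. It could act through diet, egg adherence and dropout. The questionnaires on mood, sleep, activity and diet are exposed more directly.

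**The case against.** The strongest reply is that one person's result does not identify the egg. About 40 mg of DHA per day is a modest addition, omega-3 foods may move the index in either arm, and Section 3.2 lists no EPA in the enriched egg, while the Introduction calls conversion of ALA to EPA and DHA limited. This stands. A reader might infer that the feedback discloses the allocation, or that the index rises only with enriched eggs. The documents support neither: Section 5.2 speaks only of higher exposure relative to regular eggs.

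Timing is the second reply. No dates are given, and frozen storage and batch analysis suggest that results may not exist before the end of treatment. A reader might infer that participants are effectively unblinded from week 4. That is an upper bound that needs prompt return of the week-4 results. Yet feedback given only after week 12 could not serve its stated purpose of supporting adherence, so the text needs correcting on either reading.

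Third, a reader might assume that the researcher assigned to each participant delivers the result. Section 3.3 gives that researcher follow-up and reminders under a different item and names nobody for the biomarker feedback. Staff exposure is therefore conditional on who sees the results.

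Finally, TG is objective, and diet records, recalls and egg counts capture part of the behavioural route; covariate adjustment and sensitivity analyses are planned. It would be too strong to say that nothing can be learned about the bias afterwards. These data are partly self-reported, however, and do not restore blinding.

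Feedback dates might be left to a fuller protocol. The contradiction is between two things that this article does state, and nothing in it resolves them.

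**Conclusion.** The point holds as an internal contradiction that affects the primary comparison. As written, Section 3.3 gives participants, as a motivational tool for the intervention period, a marker of the kind that the protocol expects to differ between two arms that Section 4.3 keeps blinded. The arm becomes partly inferable, and the motivational message differs by arm.

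The size is uncertain. It covers up to 120 participants and at most 8 of 12 weeks, the latter only if week-4 results are returned promptly. The best chance of a correct guess from one result is about 60% to 84% if the standardised arm difference in index change is 0.5 to 2, which is an assumption. The documents give no basis for a figure for bias in TG. Confidence is high that the sections conflict and lower on how much harm would follow.

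**What to change.** In Section 3.3, delete the feedback on omega-3 biomarkers or defer it until after database lock. State in Section 4.3 that individual omega-3 results are withheld from participants, intervention administrators, outcome assessors and data analysts until then. Keep the adherence tools that do not depend on the arm: reminders, consumption logs and egg counts. Align Section 3.3 with Sections 5.2 and 5.4 and Table 2, so that the timing of the omega-3 assays, including the red-cell index, is stated once and consistently.

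The cost is one motivational tool. Table 1 lists the trial as not yet recruiting, so the change can be made before anyone is enrolled. Optionally, ask participants in both egg arms at week 12 which egg they believe they received; this adds one question and would show how well blinding held.

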### Outcome indicators and assessment schedule

3.4

**Measurement time points:** Baseline (Week 0), and Weeks 4, 8, and 12 of the intervention.

**Baseline week:** Prior to randomization, baseline data will be collected, including general health status, physical activity, sleep quality, mood, cognitive function, dietary intake, and anthropometric measurements. Additionally, fasting antecubital venous blood samples will be obtained to assess glucolipid metabolic parameters.

### Intervention initiation and follow-up data collection

3.5

Intervention week 0 (first day of Week 2): During the baseline week, structured questionnaires will be administered to assess dietary intake, psychological status, sleep quality, physical activity, cognitive function, medical history, and concomitant medication and supplement use. Trained physicians will perform standardized anthropometric measurements, including height, weight, waist circumference, blood pressure, and body composition. Participants will be instructed to collect midstream urine samples from the first morning void using clean, sterile disposable containers, which will be transferred to pre-labeled urine collection tubes for storage and subsequent analysis. Fresh stool samples will be self-collected in sterile containers and delivered to research personnel for gut microbiota and metabolomic analyses. Fasting antecubital venous blood samples will also be obtained for outcome assessment. Participants will complete and submit three-day dietary records for verification. They will then receive eggs corresponding to their randomized group allocation, along with a “Participant Diary” for daily recording of egg consumption, supplement use, and medication intake. Diary entries and video documentation of egg consumption will be uploaded to a secure online platform to enable real-time monitoring and compliance verification by research staff. Community physicians will evaluate chronic disease complications and intercurrent symptoms based on physiological parameters, with detailed documentation of onset times, treatments, and durations to facilitate subsequent data analysis.

Intervention Weeks 4, 8, and 12: Follow-up assessments will mirror the Week 0 procedures. Fasting antecubital venous blood samples will be collected by trained medical personnel at each visit.

Participants who require medical treatment, initiate lipid-lowering therapy, or experience acute illness or exacerbation of chronic conditions during the intervention period will have the onset time, duration, and treatment measures documented in detail. Dietary assessments and other measurements will be scheduled within prespecified time windows for each study phase to minimize potential confounding effects. The study flowchart is presented in Figure 1. The schedule for enrollment, intervention, follow-up, and assessment is shown in Table 2. The intervention components and responsible personnel for the study are summarized in Table 3.

**Figure 1 F1:**
[figure not shown]
The study flowchart.

**Table 2 T2:** Time schedule for enrollment, intervention, follow-up, and assessment.

Time point	Enrollment and informed consent	Questionnaire survey	Biological samples collection (blood, urine, stool samples)	Egg consumption and medication/supplement use	Clinical measurements	Outcome evaluation
Enrollment period	√	√		√		
(Baseline week)				√		
The first day of enrollment			√	√		
Intervention phase I (Week 1–4)				√		
First follow-up (end of Week 4)		√	√	√		
Intervention phase II (Week 5–8)				√		
Second follow-up (end of Week 8)		√	√	√		
Intervention phase III (Week 9–12)				√		
Third follow-up (end of Week 12)		√	√			
Laboratory testing phase					√	
Outcome analysis phase						√

**Table 3 T3:** Details of the intervention components and responsible personnel.

Intervention components	Responsible personnel
Group A: omega-3 PUFA-enriched eggs group	
**Dietary intervention (egg consumption):** Tuesday to Saturday: One **boiled omega-3 PUFA-enriched egg daily**; Monday and Sunday: **Egg-free days** (no egg or egg product consumption); Duration: 12 weeks. **Quality control:** Eggs will be distributed weekly, with daily intake recorded. “Verbal + written” reminders will be provided on egg-free days; the diary will be verified and marked for “additional egg/egg product consumption.”	Participants (eggs consumption and diary-keeping) On-site study staff (Distribution of eggs and diaries; compliance monitoring and review)
**Adherence management:** The “Participant Diary” will be collected and reviewed daily. On the first day of each week, the next week's eggs will be distributed, and the previous week's diaries will be collected and reviewed. **Quality Control:** Missing entries will be completed on the same day; anomalies (under-consumption, over-consumption, or non-adherence to egg intake requirements) will be recorded and marked immediately. Compliance will be calculated as “actual consumption/required consumption.”	On-site study staff (Weekly distribution of eggs and collection of diaries) Remote study staff (Daily diary review and quality control)
**Follow-up preparation (Weeks 4, 8, and 12):** Consumables (urine cups, catheters, and stool specimen containers) will be distributed before follow-up visits to remind participants to fast for the next day's physical examination and to collect morning urine and stool samples. **Quality control:** Dual reminders via telephone and in person; consumable ID and distribution registration; verification of sample labels and collection times upon arrival.	**Community physicians** Remote study staff (Daily diary review and quality control)
**Follow-up assessments (Weeks 4, 8, and 12):** Questionnaire administration, physical measurements, blood and biospecimen collection; cold chain transport of samples. **Quality control:** On-site review of questionnaire completeness; defined retest thresholds for physical measurements; end-to-end traceability of samples throughout the “labeling-registration-storage-cold chain” process.	On-site study staff (Weekly distribution of eggs and collection of diaries)
**Safety monitoring:** adverse events (e.g., gastrointestinal discomfort) will be recorded and managed during follow-up visits.. **Quality control:** Severe events will be reported according to established procedures, with discontinuation/withdrawal decisions documented concurrently.	Online surveyors and community physicians
Group B: Regular eggs group	
**Dietary intervention (egg consumption):** Tuesday to Saturday: **One boiled normal fresh egg** daily; Monday and Sunday: Egg-free days; Duration: 12 weeks. **Quality control**: Identical to Group A (consistent frequency and documentation).	Participants (eggs consumption and record-keeping) On-site study staff (Distribution of eggs and diaries; compliance monitoring and review)
**Adherence management/Visit preparation/Follow-up assessments/Safety:** Procedures and quality control measures will be identical to those in Group A (daily diary review, weekly distribution, distribution of consumables and fasting reminders before follow-up at Weeks 4, 8, and 12, sample collection on follow-up days with cold chain transport).	On-site study staff (Distribution of eggs and diaries; compliance monitoring and review)
Group C: Blank control group	
**Usual diet:** Participants will maintain their habitual dietary patterns throughout the 12-week study period. **Quality control:** Potential contamination behaviors, including self-initiated consumption of eggs or egg products will be monitored through diaries and dietary surveys. These data will be used as covariates or for sensitivity analyses.	Participants (record-keeping)
**Follow-up assessments (Weeks 4, 8, and 12):** Follow-up visits and sample collection will be conducted at the same frequency as Groups A and B, including questionnaire administration, physical measurements, and blood, urine, and stool sample collection. All samples will be transported via cold chain. **Quality control:** Quality control procedures will be identical to those in Groups A and B, including on-site questionnaire review, threshold-based review of physical measurements, and end-to-end sample traceability.	On-site study staff (Distribution of eggs and diaries; compliance monitoring and review)
**Data management (all groups):** Data recording, review, and database lock. **Quality control:** Double data entry and review; source data verification for outlier detection.	Statistician

